### Physical function measures

Physical function modifications will be determined by repeated evaluations of several specific scales and questionnaires. In particular, we will use:

1. ADL scale [31]; The number of impaired ADLs was calculated considering the following six tasks: transferring from bed to chair, walking across a room, eating, bathing, using the toilet and personal hygiene.

2. IADL scale [32]; The assessment of impaired IADLs was based on the evaluation of the following four tasks: use of the telephone, use of transportations, managing medications and managing finances.

3. Short Physical Performance Battery (SPPB) [40,41]. The SPPB is a physical performance test composed by three timed subtasks: 4-meter usual gait speed, balance, and chair stand tests. Timed results from each test are scored from 0 (worst performers) to 4 (best performers) according to validated and standardized cut-points [41]. Participants unable to perform a specific SPPB subtest will result with a score of 0 (or the 99th percentile) for that part of the instrument. SPPB has shown to be associated with subclinical (e.g., inflammation, vitamin D, antioxidant status) [42,43] and clinical (e.g., comorbidity, disability, hospitalization, institutionalization, mortality) [44,45] in older persons;

4. Hand grip strength. It will be measured using a hand-held dynamometer (model Jamar). Participants will be asked to perform the task twice with each hand. The average of the best results obtained at each side will be used for the analyses. Hand grip strength has shown to be predictive of health-related events (including disability and mortality) [44,46-48];

5. *Groupes Iso-Ressources* (GIR). According to results of this scale, a special allowance (i.e., *Allocation Personalisée d'Autonomie*, APA) is allocated by the Conseil Général to functionally impaired subjects (scoring 4 or lower). Therefore, its significance is beyond a pure evaluation of physical function, but represents an easy and early indicator of the healthcare cost of an older person.

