c. When a pneumonia event will occur, physical function information collected after its onset will be compared to those previously recorded. The difference in physical function measured before and after the pneumonia event will be adjusted for the days between the event onset and the following physical function assessment. This analytical approach will allow to take into account the negative influence that the presence of a (sub)acute phase of the respiratory process may exert on physical function if the event will occur close to the evaluation. Mixed effects analysis of covariance models will also be performed to evaluate physical function modifications over time between patients who experienced a pneumonia event versus those who did not. If statistical power will be sufficient, stratified analyses will also be performed according to the severity of the pneumonia event (e.g., events requiring hospitalization versus those who did not).

For the present analyses, the sum of the results from the three SPPB categorized tests (ranging from 0 [worst physical performance] to 12 [best physical performance]) as well as the crude timed results obtained from each single assessment (in seconds) will be used for the analyses. This will allow to evaluate whether the pneumonia event will differently affect specific components of physical performance (i.e., balance, muscle strength, or gait/coordination).

Tertiary aims:

a. Chi-square and t-test analyses will be performed to describe the study population for main sociodemographic, behavioral, and clinical characteristics according to the presence/absence of a pneumonia event occurred during the INCUR project follow-up. Mann-Whitney U statistics will be used for non-normally distributed continuous variables. Normalization through log-transformation will be used for non-normally distributed study variables. Subsequent unadjusted and adjusted Cox proportional hazard models will be analyzed to identify patients’ characteristics that are able to significantly predict pneumonia events (dependent variable of interest). Among the covariates, age, gender, race, and preexisting respiratory conditions will always be considered as potential confounders. Age, gender, and race interactions will be tested for the studied relationships by adding specific interaction terms into the models. If possible, stratified analyses will be performed whereas significant interactions will be obtained.

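### The single rule for residents unable to do an SPPB subtest runs the wrong way for crude balance time if that time is seconds held; the value should be stated by subtest

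*Protocol article*

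**What the plan says.** Under Physical function measures, item 3, the article describes the SPPB as "three timed subtasks: 4-meter usual gait speed, balance, and chair stand tests". It fixes the direction of the category scores: "Timed results from each test are scored from 0 (worst performers) to 4 (best performers"). The next sentence covers inability: "Participants unable to perform a specific SPPB subtest will result with a score of 0 (or the 99th percentile"). No subtest is exempted, and the article does not say which end of performance the percentile stands for.

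The Analysis plan, secondary aim c, uses two forms of these data. One is "the sum of the results from the three SPPB categorized tests (ranging from 0 [worst physical performance] to 12 [best physical performance"]). The other is added in the same sentence: "as well as the crude timed results obtained from each single assessment (in seconds) will be used for the analyses". The stated purpose is to see "whether the pneumonia event will differently affect specific components of physical performance (i.e., balance, muscle strength, or gait/coordination"). Crude balance time is therefore a planned analysis variable. It enters the comparison before and after a pneumonia event and the mixed models comparing residents with and without pneumonia.

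**The concern.** A category score from 0 to 4 needs no percentile. The natural reading is therefore 0 for the category and the 99th percentile for the crude seconds. An upper percentile of seconds penalises only where a longer time is worse. That is so for the 4-metre walk and the chair stands. A timed balance test normally records how long a stance is held, so a longer time is better and the upper percentile is close to the best value.

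Secondary aim c asks whether pneumonia worsens physical function. Under the literal rule, the residents who lose most balance would contribute a gain to the balance component. Such residents are unlikely to be rare: Table 1 admits GIR 2 to 5, excluding only the most dependent group at entry, and residents can lose standing ability during follow-up.

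**Working it through.** The article gives no figure on this point, so there is nothing to reproduce. The check has two parts: the direction of the rule for each analysed quantity, and the size of the error under stated assumptions.

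**Direction**

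| Quantity analysed | Worst end | Value when unable (natural reading) | Effect |
|---|---|---|---|
| Category score, each subtest | 0 | 0 | Correct |
| Sum, 0-12 | 0 | 0 for that part | Correct |
| Gait time, s | Long | 99th percentile | Correct penalty |
| Chair-stand time, s | Long | 99th percentile | Correct penalty |
| Balance time, s (if seconds held) | Short, 0 s | 99th percentile | Near-best value |

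**Size of the coding error**

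Let u be the share of the group newly unable after the event and P99 the percentile assigned. Each such resident receives P99 where 0 s would express inability, so

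error in mean change = u × (P99 − 0) = u × P99.

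This does not depend on how far the residents still able decline. With u = 10%:

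- P99 = 23.5 s: 0.10 × 23.5 = 2.35, about 2.4 s upward.
- P99 = 29.9 s: 0.10 × 29.9 = 2.99, about 3.0 s upward.

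In a comparison with residents free of pneumonia, the same arithmetic applies to the difference between the groups in their newly unable shares.

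**Does the sign of the group mean change?**

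An illustrative simulation used these assumptions, none of them from the article: balance held for 0 to 30 s; everyone able beforehand; four shapes for the earlier times (beta distributions scaled to 30 s); 10% or 30% newly unable; and a decline of 0 or 3 s (not below 0 s) in the others. The P99 range above comes from these shapes. Each cell shows mean change in seconds with unable = P99, then with unable = 0 s.

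| Shape | P99 | 10% unable, no other decline | 10%, 3 s decline | 30%, no other decline | 30%, 3 s decline |
|---|---|---|---|---|---|
| Beta(1,1) | 29.7 | +1.47 / −1.49 | −1.09 / −4.08 | +4.43 / −4.51 | +2.43 / −6.46 |
| Beta(2,2) | 28.2 | +1.32 / −1.51 | −1.37 / −4.17 | +3.98 / −4.52 | +1.88 / −6.58 |
| Beta(1,3) | 23.5 | +1.60 / −0.74 | −0.72 / −3.07 | +4.80 / −2.25 | +2.98 / −4.06 |
| Beta(3,1) | 29.9 | +0.74 / −2.25 | −1.96 / −4.95 | +2.21 / −6.72 | +0.13 / −8.87 |

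- With 0 s, the mean change is negative in all 16 scenarios.
- With the literal percentile, it is positive in 12 and negative in 4. Those 4 have 10% unable and a 3 s decline in the others.
- About 99% of residents who become unable are recorded as better. This follows from the definition of the percentile.

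The mean returns to zero when the average decline among those still able equals (mean change with no other decline) / (1 − u). For 10% unable this runs from 0.74 / 0.9 = 0.82 s to 1.60 / 0.9 = 1.78 s. For 30% it runs from 2.21 / 0.7 = 3.16 s to 4.80 / 0.7 = 6.86 s.

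**The case against.** The strongest reply is that the article never says the percentile is taken from the upper tail of seconds. It is offered in parentheses beside a score of 0, just after 0 has been defined as worst. The authors may well mean the worst end of performance in every subtest. That is a fair reading of intent, so it cannot be said that the plan deliberately credits inability as good balance. But the text gives no direction, and an analyst applying it as written to a column of seconds would take the upper tail. If the worst end was meant, a statement by subtest is still needed.

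The other limits stand:

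- A reader might infer that the SPPB as a whole is reversed. It is not. The category scores and the sum treat inability as worst, and gait and chair-stand times are penalised in the right direction.
- A reader might infer that pneumonia would appear to improve balance. The documents do not support that as a general result. The sign depends on the share unable and on the decline in the others, and neither is given. The simulation also shows raw mean changes, whereas the plan adjusts for days since onset and fits mixed models.
- That a longer balance time is better comes from how the test works, not from the article.
- Which sample and visit supply the percentile is detail that an article may leave to the full protocol or analysis plan. It is not part of this point.

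**Conclusion.** The point holds in a limited form. The article states a rule rather than leaving one out, and read literally that rule runs the wrong way for one of the three crude times it covers. Two conditions are needed: balance time is recorded as seconds held, and the percentile is taken from the upper tail of seconds. Mean change in crude balance time is then too high by about the newly unable share times the percentile, illustratively 2.4 to 3.0 s for 10% newly unable. The upward error is present in every scenario examined; a change of sign in the group mean is not.

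The reach is one crude component of one of five function instruments, within a secondary aim. Incidence, costs, mortality, the SPPB sum and the other function measures are not exposed to the direction problem. This merits a should-fix grade. It is not a threat to the study's main results.

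**What to change.** State the value for inability by subtest, in Physical function measures and in the Analysis plan for secondary aim c: category score 0 for every subtest; crude balance time 0 s; 99th percentile of seconds for gait and chair-stand times only. State also that crude balance time is seconds held, so that its direction is explicit. The cost is one or two sentences and one line of programming, with no new data and no change to the visits.

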### Healthcare costs

To address the second aim of the present project related to the healthcare costs of pneumonia events in older persons living in nursing homes, the INCUR project will obtain specific data from the *Caisse Primaire d’Assurance Maladie* (i.e., the French national healthcare insurance system). In particular, the study coordinators will receive the direct costs that the healthcare system will sustain for each INCUR participant during the study period. Such figures will include total and detailed expenditures (including performed medical procedures, medications consumption, access to specific healthcare services…). As mentioned, specific parameters acting as surrogated measures of healthcare expenditures will also be directly retrieved during the INCUR clinical visits from the participants’ medical records and charts by the INCUR personnel. In particular, we will evaluate the following parameters: number and length of hospitalization events, number of major medical procedures (including admission and length of stay in Intensive Care Unit, Orotracheal intubation, mechanical ventilation), and transition to worse GIR classes. Although these (mainly clinical) parameters may not provide the exact estimation of the costs sustained by the healthcare system for the patient, they still represent reliable markers of the economical weight of the case. Moreover, since all these procedures and events have direct and negative influences on the older patient’s quality of life and functional status, their significance goes well beyond a mere financial evaluation. The collaboration with the CNAM will provide us a detailed estimation of healthcare costs charged to the public healthcare system for the management of INCUR participants. Nevertheless, the main limitation of INCUR in this context is represented by the impossibility to detect and measure costs directly sustained by the participant (and his/her family) and the impact of caregivers’ time on societal aspects.

### Sample size analyses

Mehr and colleagues [25] estimated that the incidence of nursing home-acquired pneumonia in the United States may range between 0.3 to 2.3 episodes per 1,000 resident-days. In the present study, we expect to enroll 800 EHPAD residents and follow them over a 12-month period (i.e., a total of 292,000 resident-days). Considering the attrition due to mortality (i.e., 20% per year in this setting^4^), we may expect between 70.1 and 537.3 cases according to the Meher and colleagues’ data [25]. More recently, Rothan-Tondeur and colleagues [38] reported 311 infections in a sample of 2,140 nursing home residents over a period of 28 days (from January 24 to February 20, 2005). The study was conducted defining pneumonia according to the same criteria we will implement in INCUR. Authors showed that pneumonia represented the 7% of all the cases of infections (i.e., 22 events). Translating these figures over a 365-day period (as proposed in the INCUR project) and sample size we plan to recruit (i.e., 800 participants), we obtain 107.2 pneumonia events. It might happen that attrition due to mortality (i.e., 20% per year^4^) and the spring-summer seasons (during which the pneumonia events might be fewer; i.e., additional 40% over 6 months) may further reduce such estimation. However, we believe that, even in the worst case scenario (i.e., 68.6 cases of pneumonia over one year, consistent with the minimum estimation obtained from analyses performed on the Meher and colleagues’ data [25]), it will be possible the evaluation of a sufficient number of events to successfully accomplish the INCUR study aims. The recruited sample size of 800 participants produces a two-sided 98.2% or 95.2% confidence interval with a width equal to 0,050 when the incidence of pneumonia are 10% or 15%, respectively. Such incidence rates are overestimating the outcome of interest compared to the previous study by Rothan-Tondeur et al [38]. (7%); thus, INCUR study is adequately powered to accurately estimate the incidence of pneumonia with the sample of 800 participants.

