Most of the observational studies estimating the incidence and effects of infectious diseases has been performed at the community level. Limited evidence on this topic is currently available in nursing homes and long-term care facilities which generally host older persons with higher morbidity and increased mortality risk [20,24]. Moreover, as suggested by the large variations of prevalence and incidence rates available in literature (mainly due to differences in methodological approaches, intensity of surveillance, case mix, and facility administration [25]), data from these healthcare settings are far to be definitive. Just to provide few examples about the relevance of the (currently underestimated) phenomenon in nursing home: it has been calculated that the prevalence of infections (i.e., respiratory, cutaneous, and urinary) in institutionalized older persons may range from 1.6% to 32%, and the overall incidence rates vary from 1.8 to 13.5 infections per 1,000 residents-year [26]. These figures are at least 10-fold higher than those reported in community-dwelling older persons [27]. In this context, the respiratory system is one of the most frequently affected sites for infections. The incidence of nursing home-acquired pneumonia in the United States varies between 0.3 and 2.3 episodes per 1,000 resident-days [25]. In a recent paper, Ahmed and colleagues [28] explored the hospitalization events occurring among nursing home residents in the United States, finding that pneumonia was the leading primary discharge diagnosis from the hospital (6%) and a major predictor of in-hospital mortality.

The purpose of the present article is to present the design and methodological approach of the “Incidence of pNeumonia and related ConseqUences in nursing home Resident” (INCUR) study. INCUR is an observational longitudinal cohort study aimed at estimating the incidence and economical effects of pneumonia in older persons living in nursing homes (i.e., *Etablissement d’Hébergement pour Personnes Agées Dépendantes*, EHPAD) in France.

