## Methods/design

For the INCUR project, we recruited 800 residents of 13 nursing homes randomly selected in the Midi-Pyrénées region of France. In particular, nursing homes of the region were consecutively and randomly invited at participating in INCUR. After each nursing home accepted to be involved in the study, all its residents (according to their eligibility for INCUR) were assessed by the study personnel. The recruitment was conducted up to the reaching of the final sample of 800 participants according to the predefined sample size analyses (see specific paragraph). All the nursing homes were part of a national network of institutions representative of this healthcare in France [4]. To be part of the project, the director, the coordinating physician, and the responsible for the nursing of each institution signed a formal agreement and letter of support.

The main inclusion and exclusion criteria were the constituted by the score obtained by the participant at the *Autonomie Gérontologie - Groupes Iso-Ressources* (AGGIR) scale (Table 1). This scale allows to homogeneously generate six *Groupes Iso-Ressources* (GIR) at the French national level. The resulting GIR expresses the global functional capacity of the person and drives decisions about the provision of social support from public healthcare system. Subjects with severe disability are excluded from INCUR on the basis of the worst GIR group (i.e., 1). The reason for such exclusion resides in the impossibility to determine in these patients the weight of functional loss due to a pneumonia event (primary aim d). Similarly, residents with no sign of functional impairment at the AGGIR scale (that is having the maximum GIR score of 6) are excluded due to the incapacity to perceive possible functional improvement over the follow-up.

**Table 1 T1:** Inclusion and exclusion criteria of the INCUR study

*Inclusion criteria*	*-* Residents aged 60 years and older
	*- Groupes Iso-Ressources* (GIR) ranging between 2 (included) and 5 (included). This is the French administrative tool used to rate the ability of the person to be independent; it ranges from 6 (fully independent) to 1 (fully dependent, bed-ridden)
*Exclusion criteria*	- Residents living in the participating nursing homes for less than 30 days since the baseline study visit
	- Refusal of the patient and/or the family to participate at the INCUR project

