### Analysis plan

All the analyses will consider an alpha value threshold equal to 5% as determining the statistical significance.

Primary aims:

a. Taking into account the 12-month follow-up of the study participants, we will detect all the participants experiencing a new pneumonia event. The ratio between the number of participants experiencing one or more events and the number of participants constituing the overall sample will provide the incidence of pneumonia in the sample population. Results will be presented as pneumonia cases per 1,000 resident-days, and as pneumonia events over one year. Stratified analyses will be performed according to age groups, gender, and pre-existing pulmonary disease.

Secondary aims:

a. Primary independent variable of interest for the present analyses will be the total expenditure (in Euros) that participants will cost to the healthcare system over the follow-up year. Additional secondary analyses will also consider specific aspects of the direct healthcare costs of INCUR participants such as expenses due to hospitalizations or physical therapy sessions. All these analyses will be stratified and compared according to the presence/absence of pneumonia events.

Unadjusted and adjusted analyses of covariance, logistic regression models, and multinominal logistic regression models will be performed to evaluate the means and risks of the outcome variables predicted by the absence/presence of pneumonia events occurred during the follow-up (dicothomous independent variable of interest).

b. Participating patients will be divided in two groups, according to the presence/absence of a pneumonia event experienced during the follow-up period. Then, the risk of death will be calculated and compared between the two groups. Kaplan-Meier survival curves will be provided according to pneumonia events. Moreover, adjusted Cox proportional hazard analyses taking into account age, gender, pre-existing pulmonary disease, and other possible confounders will be performed to estimate the risk of dying in patients who experienced a pneumonia versus those who did not. Follow-up will be censored at the date of death for patients dying during the follow-up, or to the last contact date for those who did not.

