A similar analytical approach will be used to evaluate specific characteristics of the EHPADs as significant determinants of pneumonia events in patients. EHPADs and patients’ characteristics might be combined in secondary analyses to evaluate the additive value of specific parameters towards the onset of pneumonia events.

b. We will perform restricted analyses in participants who will die during the follow-up (expected mortality about 20% over 12 months, that is 160 fatal events in our sample population). This subsample of participants will be divided according to the cause of death (i.e., pneumoniarelated versus other causes [expected number of cases 11.2 versus 158.8 according to Rothan- Tondeur et al [38]). Chi-square and t-test analyses will be performed to verify whether significant differences between patients dying because of a pneumonia event versus those dying for other causes exist for the following healthcare parameters: - Total expenditure (in Euros) that participants will cost to the healthcare system over the follow-up period. This datum will be obtained by the Gerontopôle from the *Caisse Primaire d’Assurance Maladie*, which has allowed the specific and exclusive release of it to the CHUToulouse. Additional analyses will also consider specific aspects of the direct healthcare costs of INCUR participants such as expenses due to hospitalizations or physical therapy sessions.

Mann-Whitney U statistics will be used for non-normally distributed continuous variables. Normalization through log-transformation will be used for non-normally distributed study variables. These analyses will consider the entire follow-up period available. Secondary analyses will also be restricted to consider the last month preceding the fatal event. In this way, we will be able to undestand whether the hypothesized higher healthcare costs of pneumonia events leading to death are distributed over time, or compressed in the very last period of life. If the statistical power will be sufficient, additional adjusted logistic and linear regression models will be performed taking into account potential confounders.

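### The stated precision for the primary incidence treats 800 residents of 13 whole homes as independent, so it is too favourable if outcomes correlate at all within homes

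*Protocol article*

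**What the plan says.** The Methods/design section describes the sample: "we recruited 800 residents of 13 nursing homes randomly selected in the Midi-Pyrénées region of France". Homes were approached in turn, and once a home had agreed, "all its residents (according to their eligibility for INCUR) were assessed by the study personnel". The sampling unit is therefore the home. The section adds that the homes belong to a national network described as representative of the sector.

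The Sample size analyses section gives the precision: "The recruited sample size of 800 participants produces a two-sided 98.2% or 95.2% confidence interval with a width equal to 0,050". The two levels belong to assumed incidences of 10% and 15% in turn. From this it concludes that the "INCUR study is adequately powered to accurately estimate the incidence of pneumonia with the sample of 800 participants". It mentions no design effect and no ICC.

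Under Analysis plan, the primary estimate is a crude proportion: "The ratio between the number of participants experiencing one or more events and the number of participants constituing the overall sample". Every analysis uses a 5% significance threshold. Tertiary aim a uses unadjusted and adjusted Cox models to find resident characteristics that predict pneumonia, and continues: "A similar analytical approach will be used to evaluate specific characteristics of the EHPADs as significant determinants of pneumonia events in patients". The only mixed model in the plan concerns physical function over time, and its random effects are not named.

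**The concern.** Residents of one home share staff, physicians, exposure to infection and recording practice. Pneumonia is identified from physician-documented signs and from charts and staff reports, so both true occurrence and detection may differ between homes. If they do, 800 residents in 13 homes carry less information about incidence than 800 residents sampled independently. With about 62 residents per home, even a small correlation matters.

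What is at stake is the published justification for the primary aim, and the honesty of the interval around the incidence estimate if it is computed in the same way. The point estimate is not affected.

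A second question follows for the home characteristics in tertiary aim a. Only 13 independent units carry information on a factor that is constant within a home. A model that counts each resident as independent would overstate that information.

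**Working it through.** **Inputs.** From the protocol: n = 800, 13 homes, full width 0.050 (half-width 0.025), incidence p = 0.10 and 0.15, alpha 5%. Assumed, because the protocol gives none: ICC = 0.005, 0.01, 0.02 and 0.05, and homes of equal size.

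**Step 1: reproduce the stated figures.** For independent residents, z = 0.025 / sqrt(p(1−p)/800) and confidence = 2Φ(z) − 1.

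- p = 0.10: 0.025 / 0.010607 = 2.357, giving 98.16% (stated 98.2%).
- p = 0.15: 0.025 / 0.012624 = 1.980, giving 95.23% (stated 95.2%).

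Both match with a design effect of exactly 1. The arithmetic is right; the independence assumption is the problem.

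**Step 2: design effect.** Mean home size m = 800/13 = 61.5. DEFF = 1 + (m − 1) × ICC = 1 + 60.5 × ICC. Effective n = 800/DEFF.

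**Step 3: precision with clustering.** Divide z from Step 1 by sqrt(DEFF) for the confidence of a 0.050-wide interval. Multiply the independent 95% width, 2 × 1.96 × sqrt(p(1−p)/800), by sqrt(DEFF) for the clustered 95% width.

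| ICC (assumed) | DEFF | Effective n | Confidence of 0.050 width, p = 10% | Same, p = 15% | 95% width, p = 10% | 95% width, p = 15% |
|---|---|---|---|---|---|---|
| 0 | 1.00 | 800 | 98.2% | 95.2% | 0.042 | 0.049 |
| 0.005 | 1.30 | 614 | 96.1% | 91.7% | 0.047 | 0.056 |
| 0.01 | 1.61 | 498 | 93.7% | 88.2% | 0.053 | 0.063 |
| 0.02 | 2.21 | 362 | 88.7% | 81.7% | 0.062 | 0.074 |
| 0.05 | 4.03 | 199 | 76.0% | 67.6% | 0.083 | 0.099 |

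Example: p = 0.15, ICC = 0.02 gives 1.980 / sqrt(2.21) = 1.332, hence 81.7%; width 0.0495 × 1.487 = 0.074.

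With 13 homes, a t quantile on 12 degrees of freedom is the natural correction. It widens the 95% intervals by a further 2.179/1.960 = 1.11, about 11%. Unequal home sizes raise the design effect further: with an assumed coefficient of variation of 0.4, DEFF at ICC 0.02 is 2.41 instead of 2.21.

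**Step 4: home characteristics, if tested at resident level.** For a factor constant within homes, the type I error of a nominal 5% test that ignores home is about 2(1 − Φ(1.96/sqrt(DEFF))):

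- ICC 0.005: 8.6%
- ICC 0.01: 12.2%
- ICC 0.02: 18.7%
- ICC 0.05: 32.9%

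A beta-binomial simulation (40,000 runs, 13 homes split 6 against 7, test on proportions) gave 12.0% to 12.4% at ICC 0.01 and 18.5% at ICC 0.02. Comparing home means in the same runs kept the error near 5%.

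**The case against.** The strongest reply is that this is a condensed article and that variance estimation is normally left to the full analysis plan. That stands for the tests. A reader might infer that home characteristics will be tested as if residents were independent, so that the false-positive rate exceeds 5% as a fact. The text says only that the approach will be similar to the Cox models, and this does not exclude a frailty term or a robust variance. The point about the tests is therefore conditional. The reply does not rescue the precision claim, which is stated in full and which no later analysis plan can alter.

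Four further readings go beyond the text:

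- **Measured variation between homes.** The Background attributes variation in rates to causes "mainly due to differences in methodological approaches, intensity of surveillance, case mix, and facility administration". That sentence concerns differences across published studies. INCUR uses one region, one case definition and centrally trained staff. The sentence makes some between-home variation plausible but gives no ICC, and nothing in the protocol favours 0.05 over a small value.
- **Significant home factors would mostly be artefacts.** A type I error of 12% or 19% is a rejection rate under the null. It is not the share of significant findings that are false.
- **All tests are inflated.** The figures in Step 4 apply only to factors constant within a home. They do not transfer to factors that vary within homes.
- **Precision must be poor.** At low ICC and lower incidence it stays close to the stated width. The protocol's worst case of 68.6 events is 68.6/800 = 8.6% if each resident has at most one event. The 95% width is then 0.044, 0.049 and 0.058 at ICC 0.005, 0.01 and 0.02 (0.049, 0.055 and 0.064 with t on 12 df). The protocol sets no threshold for accurate estimation.

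One could also restrict inference to these 13 homes, where between-home variance would matter less. The protocol presents them as randomly selected from a representative network, so that restriction is not its stated purpose.

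**Conclusion.** The concern holds for the precision statement. The 98.2% and 95.2% figures are correct only for independent residents, and the design samples whole homes. The direction is certain for any positive ICC; the size rests on an ICC that the protocol does not supply. At 15% incidence even an ICC of 0.005 takes the stated confidence below 95%; at 10% this happens by 0.01. The conclusion of adequacy is therefore unsupported as written, which is a weaker statement than saying that the study cannot estimate incidence usefully.

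For home characteristics the concern holds conditionally: the inflation arises if the ordinary Cox approach is carried over without any allowance for home.

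**What to change.** 1. In Sample size analyses, replace the 98.2%/95.2% statement and the adequacy conclusion with the expected 95% width over a stated ICC range, showing the design effect and the degrees of freedom used.
2. Compute the primary incidence interval with home as the cluster and a small-sample correction for 13 homes, such as t on 12 df.
3. For the characteristics of the homes, state that they will be tested with a home frailty term or against between-home variation, with at most 12 degrees of freedom, and reported as exploratory.

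Recruitment is complete, so the sample size is not in question. Residents were enrolled home by home, so no new data are needed. The cost is a less favourable stated precision and wider intervals. The widening is not necessarily slight: at ICC 0.05 the 95% width roughly doubles (0.099/0.0495 = 2.0), before the further 11% for t on 12 df.
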